**9**. **PHASE 3 RESEARCH METHODOLOGY**

**PHASE 3. TRANSLATION OF INPREP RECOMMENDATIONS**

The NAG will review the findings of Phase 2 against the implementation strategies developed in Phase 1. The NAG will refine implementation strategies based on findings from Phases 1 and 2, and develop and distribute key findings and recommendations to update INPREP Pathways and clinical guidelines at state and national levels. The NAG will utilise the extensive professional national networks represented across our investigatory team to enhance dissemination of the refined implementation strategies. Graphic design experts will be engaged to enhance presentation of the material for distribution. Our key recommendations will aim to allow each organisation to adopt guidelines and policy for their own context.

Knowledge translation of NPWT resources will include:

1. Conference presentations
2. Open access peer-reviewed publications
3. Targeted social media postings (twitter)
4. Podcasts
5. Blog posts
6. Champion opinion leaders

To ensure national clinical guideline recommendations are reviewed for national acceptance, findings will be presented to the clinical excellence committees for ANZBA (CIs [name], [name], [name], and [name]), PREDICT Executive (CIs [name] and [name]), and CENA Clinical Excellence Committee (CIs [name] and [name]). Moreover, a workshop detailing clinical guidelines for NPWT use in paediatric burn patients will be planned for the ANZBA Annual Scientific Meeting. Other measures to disseminate research findings will include distributing educational materials including the INPREP Pathway and an implementation manual to guide behavioural change to all Australian paediatric burns centres. Lastly, we aim to develop a web-based/digital resources that can be made available to key stakeholders to promote findings and offer a decision-making algorithm for choosing implementation strategies to supplement the clinical guideline.

**10. DATA MONITORING**

REDCap data will be backed up on the Griffith University Data Storage Service. Participants will not be identified by name, and confidentiality of patient information will be preserved. All participants details will be entered in coded format and the confidentiality of the participant will be maintained unless disclosure is required by law. Access to the data collection form will only be available to necessary members of research team and stored in accordance with data storage best practices. Any data exported from REDCap will be exported without any identifiable information, and no identifiable information data will be published. Deidentified clinician and consumer data from both phases will be kept in a locked filling cabinet, behind swipe card access only doors at the Centre for Children’s Health Research in Brisbane. An annual data management plan will be reviewed and maintained by an investigator aligned with the study.

**10.1 Data management and storage**

Electronic patient data will be backed up on the Griffith University Data Storage Service. Deidentified clinician and consumer data from both phases will be kept in a locked filling cabinet, behind swipe card access only doors at the Centre for Children’s Health Research in South Brisbane. An annual data management plan will be reviewed and maintained by an investigator aligned with the study. In accordance with the National Health and Medical Research Council guidelines, all data and samples will be stored for 15 years after completion of the study, or until the youngest person taking part in the study is 25 years old. The samples and data may also form part of future research projects conducted by the researchers, but in this case, ethics approval with appropriate data custodian and institutional approvals will be sought before the samples or data are re-used. Study findings will be published in peer-reviewed journals and presented at national and international conferences.

**12. STATISTICAL CONSIDERATIONS AND DATA ANALYSIS**

**12.1 Sample size and statistical power**

Our project follows a pragmatic design to best allow the NPWT Pathway intervention to be tailored to the site context. The study will be conducted across four state’s tertiary paediatric burns centres. All sites will start the trial in control phase with the baseline measures taken, then one site will randomly be allocated (i.e., NPWT implemented across the site) (using computer-generated, centralised randomisation) to implementation every 6 weeks, until the new intervention has been implemented across all sites at 13 months. At 13 months after implementation has occurred across all sites, adherence sustainability will be measured to inform implementation effectiveness. Using a step wedge study design, and four sites with a minimum of 100 individuals recruited from each site (recruiting patients until the capacity of the site is reached), we would be able to detect a difference of 10% in adherence rate with 94% power (5% alpha). We expect an improvement of 10% in adherence from 10% in controls to 20% in the treatment. A greater difference in adherence, with the same parameters otherwise, will result in higher power and thus the above is the minimum numbers expected. Calculations were performed with the shiny app from Hemming et al. (2015) (38). We anticipate a minimum of 120 potential patients per site, which will be more than the above estimate and thus the power of this study is expected to be >94%.

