**8.1 STUDY SETTING/LOCATION**

Phase 2 of this investigation will be conducted across four Australian paediatric burn centres within the ED, operating theatre, and burns departments. Site locations will include the following:

1. The Children’s Hospital at Westmead (CHW)

The Children's Hospital at Westmead is the largest paediatric centre in New South Wales, and provides tertiary specialist medical care for children across New South Wales, greater Australia. The CHW houses the states paediatric burns centre treating more than 800 paediatric burns patients per annum (p.a).

1. Perth Children’s Hospital (PCH)

Perth Children's Hospital is a public tertiary children's hospital located in Nedlands, Western Australia. It is Western Australia’s largest paediatric hospital and trauma centre – providing specialist medical care to children under the age of fifteen years. The PCH houses the state’s paediatric burns centre treating more than 700 paediatric burns patients p.a.

1. Queensland Children’s Hospital (QCH)

The Queensland Children's Hospital is a public tertiary children's hospital in South Brisbane, Queensland, Australia. It is the single specialist paediatric hospital for Queensland, with a catchment area extending to northern New South Wales. The QCH houses the states paediatric burns centre treating over 1000 burn injuries in children p.a.

1. Royal Children’s Hospital Melbourne (RCHM)

The Royal Children's Hospital is a public tertiary children's hospital in Melbourne, Australia. It is the major specialist paediatric hospital and trauma centre in Victoria, with a catchment extending to children from Tasmania, southern New South Wales, and other states around Australia and overseas. The RCHM houses the states paediatric burns centre treating over 500 paediatric burn patients p.a.

- 1. **STUDY POPULATION**

For Phase 2 of this investigation, participants will include paediatric patients (aged less than 18 years) presenting to the CHW, PCH, QCH, or RCHM with an acute burn. Specific eligibility criteria (inclusion and exclusion criteria) for the use of NPWT in children with acute burns will be established during Phase 1 of this investigation. Broad inclusion criteria will include children presenting to one of the four participating tertiary hospitals with an acute thermal burn injury requiring treatment from the Burns Service.

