**8.4 STUDY PROCEDURES**

Five steps will be sequentially rolled out across the 4 hospitals over 13 months: **1. Set up** ensures adequate training and collection of control and intervention data. **2. Control steps**-are usual care, i.e., standard silver dressings. **3.** **Intervention establishment** involves the research nurses (ReNs) collaborating with the NAG and local champions to promote the INPREP Pathway and delivering the companion implementation strategies. A project manager will develop a study manual and training schedule for ReNs, monitor data integrity, intervention fidelity log and collaborate with the team (ReNs and CIs) to promote intervention fidelity. **4. Implementation period** is intervention exposure. **5. Sustainability** of adherence measured. In both control and implementation steps other burn care will be as per local standards (40). Implementation education will provide evidence-based advice, but treating clinicians will determine definitive care (e.g., inpatient versus outpatient care) based on patient needs and healthcare priorities.

**Figure 2.** Steps for the multi-centre, prospective, pragmatic, stepped-wedged randomised controlled trial

[figure not shown]

**Figure 2**. Illustrates the five steps of the multi-centre, prospective, pragmatic, stepped-wedged randomised controlled trial that will be conducted across the four participating paediatric hospitals. Following initial set up, all participating sites will start the trial in control phase with the baseline measures taken, and then one site will randomly step up (computer-generated, centralised randomisation) to implementation every 6 weeks, until saturation of the implementation intervention across all sites.

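### Section 12.1: the stated 94% power (and >94%) is not reached by 100 (or 120) patients per site; even an unclustered comparison of those totals gives only about 81% (or 87%).

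*Protocol*

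**What the plan says.** Section 12.1 bases the sample size on a stepped-wedge design with "four sites with a minimum of 100 individuals recruited from each site", 10% adherence under control and 20% under the pathway, and states that "we would be able to detect a difference of 10% in adherence rate with 94% power (5% alpha". In brackets after the site minimum it adds that recruitment continues up to each site's capacity. It then reasons from a second number: "We anticipate a minimum of 120 potential patients per site, which will be more than the above estimate", and concludes that "thus the power of this study is expected to be >94" per cent. The calculator is named, but the ICC, cluster autocorrelation, number of periods and patients per site per period are not given.

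Section 8.4 describes the layout: all sites start in control, then "one site will randomly step up (computer-generated, centralised randomisation) to implementation every 6 weeks", with the rollout spanning 13 months. Section 12.2 plans a random intercept for clustering, with time available as a covariate. Section 8.3.1 defines the primary outcome as the rate of patients who received the therapy according to the pathway, so each child contributes one yes/no result.

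**The concern.** Both 100 and 120 are worded as totals per site, which makes 400 or 480 children. For 10% versus 20% that is too few for 94% power even before clustering and period adjustment are counted, and a four-site stepped wedge that adjusts for calendar period is usually much less efficient than individual randomisation of the same number. If the power figure belongs to a larger sample than the one stated, the recruitment minimum is tied to the wrong unit. A site could then meet its stated minimum while the primary comparison has far less power than claimed, and a null adherence result might be taken as failure of the pathway.

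**Working it through.** **Inputs from the protocol.** Four sites; 100 or 120 patients per site; adherence 0.10 versus 0.20 (difference 0.10); alpha 5%; one site crossing per step; all sites starting in control; random intercept with time as covariate.

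**Assumptions, because the text does not give them.** Two-sided test; 5 equal periods (baseline plus 4 steps); fixed period effects; cluster autocorrelation 1; ICC 0 to 0.20. Average outcome variance is (0.10×0.90 + 0.20×0.80)/2 = 0.125.

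**Step 1: a benchmark without ICC or periods.** For n per arm, SE = √[(0.09 + 0.16)/n] and power = Φ(0.10/SE − 1.96).
- 200 v 200: SE = √(0.25/200) = 0.0354; power = Φ(2.83 − 1.96) = 0.81 (0.80 with the pooled null variance).
- 240 v 240: SE = √(0.25/240) = 0.0323; power = Φ(3.10 − 1.96) = 0.87.
- For 94%, with pooled variance: n = [1.96√(2×0.15×0.85) + 1.555√0.25]²/0.10² ≈ 313 per arm, or 626 in all.

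**Step 2: the stepped wedge.** With m patients per site-period cell and ICC ρ, put v = (1 − ρ)×0.125/m and τ² = ρ×0.125. The standard cross-sectional variance of the treatment effect is

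Var = I·v(v + Tτ²) / [(IU − W)v + (U² + ITU − TW − IV)τ²].

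For I = 4 and T = 5: U = 4+3+2+1 = 10, W = 0+1+4+9+16 = 30, V = 16+9+4+1 = 30, so

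Var = 4v(v + 5τ²)/(10v + 30τ²).

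Worked cases:
- m = 20 (100 per site), ρ = 0: v = 0.00625, Var = 0.4v = 0.0025, SE = 0.050, power = Φ(2.00 − 1.96) = 0.52.
- m = 20, ρ = 0.05: v = 0.00594, τ² = 0.00625, Var = 0.00358, SE = 0.0598, power = Φ(1.67 − 1.96) = 0.39.
- m = 100, ρ = 0.05: v = 0.00119, Var = 0.000773, SE = 0.0278, power = Φ(3.60 − 1.96) = 0.95.

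| Patients per cell | Total | ICC 0 | 0.01 | 0.05 | 0.10 | 0.20 |
|---|---|---|---|---|---|---|
| 20 (100 per site) | 400 | 0.52 | 0.44 | 0.39 | 0.39 | 0.42 |
| 24 (120 per site) | 480 | 0.59 | 0.49 | 0.44 | 0.45 | 0.48 |
| 100 (500 per site) | 2,000 | 0.99 | 0.96 | 0.95 | 0.96 | 0.97 |

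**Step 3: can 94% be recovered from the stated totals?**
- One-sided alpha: at most 0.64 (100 per site) or 0.71 (120).
- No period adjustment, ICC 0–0.20: 0.754–0.811 (100) or 0.824–0.875 (120).
- Nine periods instead of five: 0.28–0.32 (100) or 0.33–0.37 (120).
- In the 4×5 design, two-sided, 94% is reached only at an ICC of about 0.81 (100 per site) or 0.77 (120).
- A simulated logistic analysis with fixed site and period effects gave 33%, 39% and 93% for 20, 24 and 100 per cell, in line with the table.

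**Step 4: where might 94% come from?** Taking 100 as the cell size gives 0.95–0.96 at ICC 0.01–0.10 (0.944–0.953 with pooled variance 0.1275). Exactly 94% needs 92, 96 and 92 per cell at ICC 0.01, 0.05 and 0.10, but 62 at ICC 0 and 82 at ICC 0.20. With autocorrelation 0.8 and ICC 0.05, 100 per cell gives only 0.72.

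**Step 5: volumes if 100 per cell was meant.** Section 8.1 gives floors of 800, 700, 1,000 and 500 burns a year (the last as "treating over 500 paediatric burn patients p.a"). In 6 weeks (×6/52) that is about 92, 81, 115 and 58, before eligibility and consent.

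**The case against.** The best defence is that 100 is a floor: the protocol plans "a minimum of 100 individuals recruited from each site (recruiting patients until the capacity of the site is reached"). At the section 8.1 volumes, 13 months would bring about 3,000×13/12 = 3,250 burns. Spread over five equal periods, power would be about 0.9 or higher if half enrolled and roughly 0.7 to 0.9 if 30% did (ICC 0–0.10). This stands to the extent that a reader might infer that the trial as run has less than an even chance of detecting its target effect, and the documents do not support that. Final enrolment is unknown, and even at the stated totals power exceeds one half at ICC 0. The defence does not rescue the text, however, because section 12.1 attaches 94% to the minimum of 100 and >94% to an expected 120.

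A second objection is that the percentages depend on an assumed layout. That is right. Five 6-week periods last 30 weeks, not 13 months, and Figure 2, which may show the layout, could not be read in the copy available. The 39–52% and 44–59% are therefore conditional. The unclustered benchmark needs no period layout or ICC and already falls short.

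Third, a reader might infer from the 6-week volumes that three of the four sites cannot supply 100 per period. The documents do not establish this: the volumes are floors, and periods may be longer than 6 weeks. Five equal periods over 13 months would see about 173, 152, 217 and 108 burns per site before eligibility and consent.

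**Conclusion.** The point holds as a mismatch between the stated sample and the stated power. With 400 or 480 children and one outcome each, 94% and >94% are not reached at any plausible ICC, and unclustered 1:1 comparisons give about 80–81% and 87%. Under the labelled assumptions (4×5 equal cells, fixed period effects, autocorrelation 1, two-sided 5%, ICC 0–0.20), power is about 39–52% and 44–59%.

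Two further inferences should be resisted. That a per-period cell size was reported as a site total is plausible, since 100 per cell comes within about 2 points of 94% at ICC 0.01–0.10, but the protocol does not show it. Nor can one detectable difference be written in as a replacement. With variance held at 0.125 and 80% power (2.80×SE), it runs from 14.0 to 16.8 points at 100 per site and 12.8 to 15.4 at 120 over ICC 0–0.20, and it is higher if the variance is updated for the larger effect.

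**What to change.** Rerun the calculation and state in section 12.1 the number and length of periods, patients per site per period, ICC, cluster autocorrelation and sidedness used. Replace 94% and >94% with the power those inputs give for the stated minimum (100 per site) and anticipated number (120 per site), or give the detectable difference computed from the same inputs. A short range over ICC and autocorrelation would be enough.

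If 100 was meant per site per period, say so, express the recruitment minimum and the anticipated 120 in that unit, and check both against the section 8.1 volumes for the actual period lengths (about 58–115 burns per site if periods are 6 weeks, at the floor volumes and before eligibility and consent).

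The cost is one rerun of the calculator and a few sentences of protocol text. No extra enrolment is asked for; the stated power becomes less favourable if the per-site totals stand.

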**12.2 Statistical analysis methods**

Generalised Linear Mixed Models (fitting a random intercept to account for clustering, random effect) and Generalised Estimating Equations (using the individual as the clustering unit) will be used to compare the effect of switching from the usual care to INPREP condition on primary and secondary outcomes. Specifically, an appropriate protocol for model selection based on Zuur *et al*. (2009) will be applied (49). This analysis approach is able to account for potential temporal trends, using time as a covariate, in addition to clinical explanatory variables (total body surface area, age, gender), which will be included in each model. It should be noted that other covariates, such as time, could be used as random effects in the mixed models.

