We propose to facilitate the early implementation of NPWT into ED burn care practice to provide Australian children access to evidence-based treatment that may improve clinical outcomes and reduce healthcare costs. Partnering with Australia’s four major paediatric burns centres (The Children’s Hospital at Westmead, Perth Children’s Hospital, Queensland Children’s Hospital and Royal Children’s Hospital, Melbourne), we will co-design implementation strategies tailored to the complex acute burn care setting and evaluate the effectiveness of implementation. We hypothesise that the facilitated implementation will result in better adherence to early NPWT application in acute burn care settings (ED/burns centres). Leveraging previous, successful collaborations and international expertise of the CI team, results from this study will transform policy and practice to improve outcomes for Australian children.

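### With only four hospitals, a random intercept for clustering lets the primary test run at about 7-7.5% instead of 5% when hospitals differ moderately; hospital as a fixed effect restores about 5%

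*Protocol*

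**What the plan says.** Section 12.2 names two analyses for the primary and secondary outcomes. The first is a generalised linear mixed model, "fitting a random intercept to account for clustering, random effect". The second is "Generalised Estimating Equations (using the individual as the clustering unit"). Time, burn area, age and gender enter as covariates. A published model-selection procedure is to be followed, and time may also be made a random effect. The level of the random intercept is not stated. Whole hospitals cross from control to implementation (Sections 8.4 and 12.1), so hospital is the natural reading.

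Section 12.1 fixes the size: "four sites with a minimum of 100 individuals recruited from each site", adherence moving "from 10% in controls to 20% in the treatment", "with 94% power (5% alpha"). No ICC is given. Section 12.2 mentions no fixed hospital effect, no small-sample correction and no rule for a hospital variance estimated as zero.

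**The concern.** A random intercept adjusts for hospital only as far as its variance can be estimated, and here it is estimated from four values. With about 100 children per site and 10% adherence, the estimate often falls on zero although hospitals truly differ. The fitted model then has no site term. It counts differences between hospitals as evidence about the pathway and understates the standard error. Even when the estimate is positive, a variance from four units is imprecise, and a normal reference ignores that.

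At stake is the 5% level of the primary adherence test. The problem does not depend on time being mis-specified or on sites drifting, so getting those right would not cure it. The companion GEE is no safeguard, because clustering on the individual makes no adjustment for hospital.

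**Working it through.** **The plan's own figure.** With 400 children split 200 v 200, a simple two-proportion test of 10% v 20% has null SE √(2×0.15×0.85/200) = 0.0357 and alternative SE √((0.09+0.16)/200) = 0.0354. Then z = (0.10 − 1.96×0.0357)/0.0354 = 0.85, which is 80% power. A time-adjusted stepped wedge (Hussey-Hughes variance, 4 sequences × 5 periods, ICC 0-0.20, cluster autocorrelation 1 or 0.8) gives 24-52%. With the anticipated 120 per site ("We anticipate a minimum of 120 potential patients per site") these become 87% and 26-59%. A value near 94% appears only if 100 is read as per site per period (about 95% at ICC 0.01-0.10). So 94% is not reproduced as written. The present point does not rest on it; what is tested below is the 5% level.

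**Model simulated, with no pathway effect.** logit P(adherent) = period effect + θ·(implementation) + uᵢ, with uᵢ ~ N(0, σ²).
- From the protocol: four sites, 100 children each, 10% adherence, one site crossing at a time in random order, and "All sites will start the trial in control phase with the baseline measures taken".
- Assumed: five equal periods of 20 children per site, a two-sided test, and a range of σ, because no ICC is given.
- No secular trend, no drift, no patient covariates.
- Fitted by maximum likelihood with categorical periods; reject if |θ̂/SE| > 1.96. The comparator replaces uᵢ by three hospital indicators.

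**Scale of σ.** At 10% adherence ICC ≈ 0.10×0.90×σ², so σ = 0.25, 0.5 and 0.8 give about 0.006, 0.02 and 0.06. One SD of 0.5 either side of logit(0.10) = −2.197 gives −2.697 and −1.697, that is 6.3% and 15.5% adherence.

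**False-positive rates from repeated runs.** Monte Carlo SE is √(0.07×0.93/n): about 0.4 points at 4,800 or 5,000 trials and 0.2 at 20,000.

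| σ | Variance estimated as zero | Random intercept, 4,800 trials | 5,000 trials | 20,000 trials | Fixed hospital effects |
|---|---|---|---|---|---|
| 0.25 | about 62% | 6.2% | 5.5% | 5.8% | 4.5-5.0% |
| 0.5 | about 33% | 7.5% | 7.4% | 6.9% | 4.5-5.1% |
| 0.8 | about 15% | 7.5% | 7.5% | 7.6% | 4.5-5.2% |

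A further 6,000 trials per scenario, indexed by ICC, with 100-120 children per site and time categorical or linear, gave for the random intercept: 4.3-4.8% at ICC 0, 6.1-6.6% at 0.01, 6.9-7.7% at 0.02, 7.4-7.8% at 0.05 and 6.8-7.5% at 0.10. Fixed hospital effects gave 4.3-5.5% over the same range. A likelihood-ratio test did not cure the excess (6.6-7.7% at ICC 0.02 and above).

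**Where the excess arises.**
- σ = 0.5: false positives were 12.7% in zero-variance trials and 4.9% in the rest. Check: 0.33×12.7 + 0.67×4.9 = 7.5%. Excess over 5%: 0.33×7.7 = 2.5 points from zero-variance trials and 0.67×(−0.1) = −0.1 from the rest. Essentially all of it comes from the vanished site term.
- σ = 0.8 (5,000 trials): 16.2% and 5.9%. Excess: 0.15×11.2 = 1.7 points and 0.85×0.9 = 0.8 points, so about two thirds.
- 100 children per site-period, ICC 0.05, categorical time: variance zero in 3.7% of trials; 20.7% and 7.9%. Excess: 0.037×15.7 = 0.6 points and 0.963×2.9 = 2.8 points. Here the main cause is the imprecise variance and the normal reference.

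**No hospital term at all.** The false-positive rate is 13-35% at ICC 0.02-0.10. This shows what an analysis that ignores hospital is exposed to.

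**The case against.** The strongest reply is that the reference distribution is at fault and not the random intercept. With 20 site-periods less 4 sites, 4 further periods and 1 treatment term there are 11 degrees of freedom. Referring the random-intercept statistic to t with 11 df gave 3.2%, 4.1% and 4.6% at σ = 0.25, 0.5 and 0.8, with power for 10% v 20% of 36% (σ = 0.25) and 32% (σ = 0.5), against 34% at both with fixed hospital effects. The protocol names neither a Wald test nor a reference distribution, and such details are often left to a statistical analysis plan. This stands in part: a t reference does control the level, so a random intercept is not invalid in itself. But the protocol commits to the intercept and to no correction, and fixed effects come closer to 5% at no loss of power at σ = 0.5.

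A reader might infer a flat 7-8% inflation. The documents do not support that. They give no ICC, and the inflation is about one point at σ = 0.25 and absent near ICC 0 (4.3% at σ = 0.1). A reader might also infer that frequent zero estimates and large inflation go together. They do not: zero estimates are most frequent where the inflation is smallest.

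The hospital level is a reading, since Section 12.2 does not name it, and the model-selection step means the model simulated is one candidate. Nothing in that step protects the site term.

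Finally, the "four major paediatric burns centres" are the whole trial setting, but Section 12.2.2 models roll-out to all specialist paediatric hospitals in Australia and Section 9 plans national recommendations. A fixed effect limits the trial's formal inference to these four. That limit is real. However, four hospitals support only a weak estimate of between-hospital variance under either model.

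**Conclusion.** The concern holds in conditional form. If the intercept is for hospital and an uncorrected Wald test is used, the primary test has a false-positive rate of about 7-7.5% when the between-hospital logit SD is about 0.5 or more (ICC about 0.02 or more), about 6% at SD 0.25, and no inflation near ICC 0. Section 2.3 says that NPWT use differs between Australian services. That makes an ICC near zero unlikely but does not give its size.

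The result rests on equal periods, 100-120 children per site, 10% adherence, normal hospital effects and no patient covariates in the simulation. The excess is modest, about 2 to 2.5 points at moderate ICC, but it falls on the primary test and a change of wording removes it.

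**What to change.** In Section 12.2, fit hospital as a fixed effect (three indicator terms) together with fixed period effects in the primary model. Keep the random-intercept model as a sensitivity analysis, name hospital as its level, and refer its statistic to a t distribution with few degrees of freedom. Say in advance what is done if a hospital or period has no adherent child, since its fixed effect could not then be estimated.

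The cost is wording only; no extra data are needed. Nominal power for 10% v 20% at 100 children per site falls from about 38-45% to about 34%. Much of that fall is the excess false-positive rate: once the random-intercept test is held to its level with the t reference, its power is 36% at SD 0.25 and 32% at SD 0.5. The report should state that inference is to these four hospitals and that any national extrapolation rests on the modelling in Section 12.2.2.

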**8.3 STUDY OUTCOMES**

**8.3.1 Primary Outcome**

1. INPREP Pathway adherence: rate of patients who received NPWT (according to eligibility and duration of application defined within the INPREP Pathway)

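### Section 12.2 puts both a mixed model and a GEE clustered on the child on the primary adherence outcome without saying which decides, and the GEE as written ignores the randomised hospital

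*Protocol*

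**What the plan says.** Protocol section 12.2 names two methods in one sentence. The first is "Generalised Linear Mixed Models (fitting a random intercept to account for clustering, random effect"), with the cluster unit left unnamed. The second, a GEE that takes the individual as its cluster, is joined to it directly: "random effect) and Generalised Estimating Equations (using the individual as the clustering unit) will be used to compare the effect of switching". Both are to assess the switch "from the usual care to INPREP condition on primary and secondary outcomes"; the sentence neither divides the outcomes between them nor ranks them.

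The section then refers to "an appropriate protocol for model selection based on Zuur" and a citation, without giving a criterion. It puts time in as a covariate, adds "clinical explanatory variables (total body surface area, age, gender), which will be included in each model", and remarks that "other covariates, such as time, could be used as random effects in the mixed models".

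Section 8.3.1 defines the primary outcome as "INPREP Pathway adherence: rate of patients who received NPWT", subject to the pathway's eligibility and duration rules. That is one yes/no value per child. Section 12.1 gives one error rate: "we would be able to detect a difference of 10% in adherence rate with 94% power (5% alpha"). Neither section says which test decides.

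**The concern.** The hospital is the unit randomised to a crossover date. In a one-site-per-step schedule the first hospital to cross spends most of the trial under INPREP and the last spends least, so baseline differences between hospitals feed into the treatment contrast unless hospital is modelled. A mixed model with a hospital random intercept addresses this. A GEE clustered on the child does not: with one value per child it is ordinary logistic regression with robust standard errors.

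The two methods also target different quantities for a binary outcome under a logit link: a hospital-conditional odds ratio and a population-averaged one. A borderline primary result could therefore be significant or not depending on which model is reported, and one of the two permitted models does not hold the stated 5%.

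**Working it through.** **Inputs.** From section 12.1: four hospitals, at least 100 children each, adherence 10% against 20%, 5% alpha (taken as two-sided; sidedness is not stated), one hospital crossing every 6 weeks. Assumed: five periods (one baseline and four steps), hence 100/5 = 20 children per hospital-period; a random intercept at hospital level; site log-odds SD 0.3 or 0.6, because the protocol gives no ICC. On the latent scale, ICC = SD²/(SD² + 3.29): 0.09/3.38 = 0.027 and 0.36/3.65 = 0.099.

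**The plan's own figure, 94% power.** For a stepped wedge with fixed periods and a random site effect, with I = 4 sites and T = 5 periods,

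Var = Iσ²(σ² + Tτ²) / [(IU − W)σ² + (U² + ITU − TW − IV)τ²].

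Here U = 4+3+2+1 = 10 counts the intervention cells, W = 0+1+4+9+16 = 30 and V = 16+9+4+1 = 30. The average binomial variance is (0.09 + 0.16)/2 = 0.125.

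- 20 per cell, ICC 0: σ² = 0.125/20 = 0.00625; Var = 4σ²/10 = 0.0025; SE 0.05; power Φ(0.10/0.05 − 1.96) = 52%. At ICC 0.01 to 0.10 it is 39% to 44%.
- 100 per cell, ICC 0.05: σ² = 0.0011875, τ² = 0.00625; Var = 0.000154/0.199 = 0.000773; SE 0.0278; power Φ(3.60 − 1.96) = 95%.

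So 94% is approached only if 100 means per hospital per period. That is a separate question and does not affect this point.

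**The two candidate tests.**

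- Mixed model: logit p = period effect + θX + u, with u ~ N(0, SD²) by hospital.
- GEE as written: the same fixed part without u, with variance A⁻¹BA⁻¹, where A = Σp(1−p)xx′ and B = Σ(y−p)²xx′ sum over children. Hospital appears nowhere.

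In this layout the first hospital to cross has 4 of 5 periods under INPREP and the last has 1 of 5, so treatment is partly confounded with hospital.

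**Simulation**, 500 trials per setting, 10% control adherence, periods as fixed effects, no patient covariates:

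| | Site SD 0.3 | Site SD 0.6 |
|---|---|---|
| No effect: mixed model rejects | about 6% | about 6% |
| No effect: GEE as written rejects | 10% | 18% |
| No effect: either rejects | 10% | 19% |
| 10% to 20%: one significant, the other not | 13% | 24% |

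Monte Carlo standard errors: √(0.10×0.90/500) = 1.3 points and √(0.18×0.82/500) = 1.7 points for the GEE; √(0.06×0.94/500) = 1.1 points for the mixed model.

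**Repeat runs of the same layout.**

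- 600 null trials: GEE alone 9.8% and 18.5%; either test 10.2% and 19.2%. The second test adds 0.4 and 0.7 points.
- About 1,000 null trials per setting with a Wald test for the mixed model, at latent ICC 0, 0.01, 0.05 and 0.10: mixed model 4.3%, 4.7%, 6.8%, 8.5%; GEE 5.2%, 5.1%, 12.6%, 19.6%; either 5.8%, 6.1%, 13.2%, 21.2%. The second test adds 0.6, 1.0, 0.6 and 1.6 points.
- Disagreement at the planned effect: 9% to 21% over SD 0.3 to 0.6 in one run, and 10.2% at SD 0.3 in another.

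**The case against.** **This belongs in the SAP.** Naming model families in a protocol and the deciding model in a SAP is common, and the SAP is not at hand. That would answer a silence. Here the protocol itself commits to two methods for the primary outcome, and one of them, followed as written, has the wrong error rate.

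**The GEE may be meant for repeated measures.** Appendix 5 has pain scores and percentage re-epithelialised at successive dressing changes, and clustering on the child fits those. This is a plausible intent, and it shapes the fix. The sentence does not say so, and it covers the primary outcome.

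**Model selection may lead to one final model.** It may, but the section gives no criterion and does not say that the procedure chooses between the mixed model and the GEE. A data-driven choice would in any case not fix the test in advance.

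**Stronger readings that the protocol does not support.** A reader might infer that success will be claimed if either test is significant; no passage says this. A reader might also blame the inflated error on having two tests. The figures do not bear that out: nearly all of it is already present in the child-clustered GEE alone. Nor does disagreement mean opposite directions of effect; it means one p-value below 0.05 and the other above.

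**Correcting the GEE's cluster would be enough.** It would not. Two unranked tests would remain, and a sandwich estimator with four clusters is itself unreliable: with a t(3) reference it rejected 9% and 11.5% under no effect at SD 0.3 and 0.6.

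**Conclusion.** The point holds as an unresolved choice between two methods, one of which is unsuitable for adherence. Over the assumed site SDs of 0.3 to 0.6, the GEE as written rejects a true null in about 10% to 18% of trials against about 6% for the hospital-level mixed model. Having both available adds under 1 point in the main simulation and 0.4 to 1.6 points in the repeat runs. At the planned effect the reported significance depends on the model in about 13% to 24% of trials.

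These sizes rest on the assumed site variation, five periods and 20 children per cell. If hospitals hardly differ (ICC 0 to 0.01), the GEE stays near 5% and the harm reduces to the open choice. The mixed model alone also runs a little above 5% when hospitals differ, so naming it without a small-sample correction would not fully restore the stated alpha.

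**What to change.** State in section 12.2 that the primary test is the treatment coefficient from one logistic mixed model with a hospital random intercept and fixed period effects, at two-sided 5%, with a named small-sample correction or a permutation check suited to four hospitals. With one hospital per step there are 4! = 24 possible orders, so the smallest attainable permutation p-value is 1/24 = 0.042; permutation therefore serves better as a check than as the deciding test.

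Any GEE for adherence becomes a sensitivity analysis, clustered by hospital, reported as an estimate and confidence interval, and does not decide the trial. Keep a GEE clustered on the child only for outcomes measured repeatedly within a child, and name one deciding model for each secondary outcome too.

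The cost is a few sentences. Both models can still be run. What is lost is the option to choose between them afterwards, and slightly lower nominal power from the small-sample correction.
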